#### 2.7.2. Rewards for Participation

Randomized participants will not receive any type of financial incentive, although all will receive the lifestyle intervention program and manual (the control group will receive it after completing the 12-month assessments).

## 3. Measurements

### 3.1. Body Composition

#### 3.1.1. Anthropometry

Subjects will have their weight and height measured in bathing suits and no shoes to the nearest 0.01 kg and 0.1 cm, respectively, with a stadiometer (Seca, Hamburg, Germany). Body mass index will be calculated using the formula [weight(kg)/height^2^(m^2^)] and the cut-off points of the World Health Organization (WHO) will be used [45]. Waist circumference will be measured immediately above the iliac crest and reference values proposed by WHO will be used [46]. Triceps, subscapular, abdominal, supra-iliac, thigh, and calf skinfolds and arm, thigh, and calf circumferences were assessed by a technician accredited by ISAK (International Society for the Advancement of Kinanthropometry), as described elsewhere [47].

#### 3.1.2. Dual-Energy X-ray Absorptiometry

To estimate total and regional fat mass (FM) and fat-free mass (FFM), dual-energy X-ray absorptiometry (DXA; Hologic Explorer-W, Waltham, MA, USA) will be used. A whole-body scan will be performed and the attenuation of X-rays pulsed between 70 and 140 kV synchronously with the line frequency for each pixel of the scanned image will be measured. Total abdominal fat, which includes intra-abdominal fat plus subcutaneous fat, will be distinguished using DXA by identifying a specific region of interest (ROI) within the analysis program. Specific DXA ROIs for abdominal regional fat will be defined as follows: from ROI 1, the upper edge of the second lumbar vertebra (approximately 10 cm above the L4 to L5) to above the iliac crest and laterally encompasses the entire breadth of the abdomen, thus determining total abdominal fat mass [48].

#### 3.1.3. Bioimpedance Analysis (BIA)

Before the test, subjects will be instructed to lie in a supine position with their arms and legs abducted at a 45 angle for 10 min. The measurements assessed by the bioimpedance devices (described below) will be performed in a random order (time difference 30 s). Four electrodes will be placed on the dorsal surfaces of the right foot and ankle and the right wrist and hand. A 240 μARMS alternating current at 50 kHz will be introduced into the distal electrode of each pair (source electrode), and the voltage drop across the body will be measured using the proximal electrode (detector electrode). Low-impedance electrodes (25.74 Ω) (AKERN-BIATRODES/0ELB) will be used in both multispectral and single frequency devices.

#### 3.1.4. Multispectral Frequency Bioelectrical Impedance

Bioelectrical impedance spectroscopy analysis (BIA; Xitron Technologies model 4200 B, San Diego, CA, USA) will be used to assess total-body water (TBW) and its compartments. This impedance spectra is modelled with the Cole–Cole cell suspension model [49] to derive a theoretical impedance at zero and infinity frequency, based on a non-linear curve fitting from the measured resistance and reactance. Intracellular water and extracellular water will be predicted from the Hanai mixture theory [50], and TBW will be estimated by the sum of intracellular water and extracellular water.

#### 3.1.5. Single-Frequency Bioelectrical Impedance

Whole body R, Xc, and phase angle will also obtained by BIA using a single-frequency, phase-sensitive 50 kHz (BIA-101, RJL/Akern Systems, Firenze, Italy). Prior to each test, the technical validity of SF-BIA instrument will be determined with a precision circuit (R = 383 Ω and capacitance = 46 Ω). Measured resistance and reactance values will be within the tolerance of the precision circuit (≤10 Ω and ≤5 Ω, respectively).

#### 3.1.6. Resting Energy Expenditure

Assessment of REE will be performed in the morning when fasted (8.00–10.00 a.m.). All measurements will be performed in the same room at environmental temperature and humidity of approximately 22 °C and 40–50%, respectively. The MedGraphics CPX Ultima (MedGraphics Corporation, Breezeex Software) indirect calorimeter will be used to measure breath-by-breath oxygen consumption ($\dot{V}O_{2}$) and carbon dioxide production ($\dot{V}CO_{2}$) using a facial mask. One trained technician will conduct all measurements. The oxygen and carbon dioxide analyzers will be calibrated in the morning before testing, using known gas concentration. The flow and volume will be measured using a pneumotachograph calibrated with a 3L-syringe (Hans Rudolph, inc.TM). Before testing, participants will be instructed about all the procedures and asked to relax, breathe normally, not to sleep, and not to talk during the evaluation. Total rest duration will be 45 min, participants will lie supine for 15 min covered with a blanket and the calorimeter device will then be attached to the mask and breath-by-breath VO_2_ and VCO_2_ will be measured for a 30-min period.

The first and the last 5 min of data collection will be discarded and the mean of a 5-min steady state interval between the 5 and 25 min with a respiratory exchange ratio (RER) between 0.7 and 1.0 will be used to determine REE. Steady state will be defined as a 5-min period with ≤10% CV for $\dot{V}O_{2}$ and $\dot{V}CO_{2}$ [51]. The mean $\dot{V}O_{2}$ and $\dot{V}CO_{2}$ of 5-min steady states will be used in the Weir equation [52] and the period with the lowest REE will be considered for data analysis.

#### 3.1.7. Adaptive Thermogenesis

In order to predict REE at baseline, a gender-specific regression equation using FFM and FM as the independent predictors will be generated. This equation will then be used to predict REE at four months and after a 12-month follow-up, using the measured values of FM and FFM at these time points. To disclose any adaptations in REE not accounted for by changes in FFM, the adaptive response will be assessed as 1 min the ratio between the actual to the expected/predicted REE, multiplied by 100. Positive values indicate a decrease in REE beyond that expected by changes in body composition (actual REE below predicted REE) whereas negative values represent a change in REE equal to or greater than the predicted REE (actual REE higher than the predicted REE) [20]. The magnitude of the adaptive thermogenesis will be further analyzed by examining leptin levels and thyroid function.

#### 3.1.8. Energy Intake

When total energy expenditure (TEE) is obtained in conjunction with measured body composition, then two terms of the EB equation are known, namely EB and energy expenditure (EE). From the previous equation, we can estimate average energy intake during the course of the study. The magnitude of compensation will be calculated as the difference between achieved energy imbalance and EE. Three-day food records (with one-weekend day) will also be collected to characterize macronutrient composition of the diet in the three assessment sessions using a software package (Food Processor SQL, ESHA Research, Salem, OR, USA) by a registered dietitian. Comprehensive written instructions using specific guidelines, including pictures of portion sizes used for a better recording of food intake, and examples of common errors in recording dietary intake combined with face-to-face debriefing sessions will ensure accurate food records collection. At the end of the recording period, a registered dietitian will review the record with the participant to clarify potential omissions and ambiguities and to assure that additional information is provided to improve the accuracy of the macronutrient composition of the diet.

### 3.2. Free-Living Physical Activity and Energy Expenditure

#### 3.2.1. Accelerometry

All participants will be asked to wear an accelerometer ActiGraph GT3X+ (ActiGraph, Pensacola, FL) to assess the amount of activity expressed as minutes per day spent in different intensities. The accelerometer will be placed on the right hip, near the iliac crest, during waking-hours, and requested to be removed only during water-based activities such as showering and swimming [53]. The device activation, download, and processing will be performed using the software Actilife (v.6.9.1). The cutoff values used to define the intensity of PA and therefore to quantify the mean time in each intensity (sedentary, light, moderate, or vigorous) will be as follows: sedentary: <100 counts·min^−1^; light: 100–2019 counts·min^−1^; moderate: 2020–5998 counts·min^−1^ (corresponding to 3–5.9 METs); vigorous: ≥5999 counts·min^−1^ (corresponding to ≥6 METs) [54]. Participants will be included if they had a total of at least three valid days of accelerometer data. A valid-day will be defined as having 600 or more minutes (≥10 h) of monitor wearing, corresponding to the minimum daily use of the accelerometer [55]. Apart from accelerometer non-wearing-time (i.e., when it is removed for sleeping or water activities), periods of at least 60 consecutive minutes of zero activity intensity counts will also be considered as non-wearing-time [56]. An Actigraph break will be considered as any bout of time in which the accelerometer count rises up to or above 100 counts·min^−1^ and which stays within the light-intensity physical activity (LIPA) range (<2020 counts·min^−1^). There are no cutoffs for the sedentary-time using the three-axial information from this new generation Actigraph GT3X+ accelerometer; therefore, we will use the previous cutoffs, which utilize the vertical-axis information only.

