In this regard, interventions that support autonomous motivation for physical activity may foster increased engagement in self-regulation techniques and positively affect lifestyle health behaviors [35]. A systematic review on effective behavior change interventions designed to promote PA and healthy eating [36] clearly supported the inclusion of multiple self-regulatory techniques, specifically self-monitoring of behavior in combination with prompt intention formation, prompting specific goal setting, providing feedback on performance, and prompting review of behavioral goals [37]. Therefore, the inclusion of self-regulatory skills within autonomy-supportive educational sessions brings added value to encourage the adoption of energy balance behaviors.

This paper describes the protocol for a randomized controlled trial, which aims to evaluate the effectiveness of the Champ4Life program in supporting former athletes to improve their lifestyles versus a waiting list control group that is offered the program after the 1-year follow-up. The primary aim of the trial is to determine whether Champ4Life can help inactive former athletes aged 18–65 years with a body mass index (BMI) ≥25 kg/m^2^ to reduce total and abdominal fat mass over 12 months. Secondary outcomes include cardio-metabolic blood biomarkers (e.g., glucose, insulin, HbA1c, lipids, liver function), adaptive thermogenesis blood-derived indices (leptin and thyroid function), weight and waist circumference, improvement in other body components (fat-free mass, water compartments), resting systolic and diastolic blood pressure, physical fitness (e.g., cardiorespiratory fitness, strength), free-living PA, sedentary time, energy balance regulation, eating self-regulation markers, and quality of life.

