Subjects will attend 12 educational sessions aimed at promoting a healthy lifestyle, in groups of 10–15 participants, for approximately four months. Sessions will last 60–90 min and will include educational content and practical application in-class exercises in the areas of PA and exercise, diet and eating behavior, and behavior modification [36]. The first session named “ABC of weight loss” is an initial session aimed at discussing body composition components (body fat and fat-free mass) and how energy balance and its components (energy expenditure and energy intake) are regulated. It will also be discussed the impact of weight-sensitive sports on body weight regulation and health-related issues [40,41]. In the second session, given by a psychologist, eating behavior dysregulation, metabolic and behavioral compensatory mechanisms will be discussed and strategies to distinguish real from “emotional” hunger and emotional eating will be the central topics. In the 3rd session, basic nutrition concepts such as the three macronutrients (protein, lipids and carbohydrates), vitamins and minerals will be addressed. We will also discuss the food wheel based on the Mediterranean diet and the healthy eating pyramid. In the fourth session, the benefits of being active will be the main topic and some recommendations will be given in order to increase daily routine PA and structured physical activity. The fifth session will be the extension of Session 2 and a dietitian will present several types of diets, its pros and cons, and lead a discussion/reflexion about which diet is the best for each type of participant. Sedentary behavior will be the main topic of the sixth session, presenting strategies to reduce sedentarism. On the seventh and eighth sessions, the pros and cons of fasting, meal frequency and its influence on weight loss, and which foods are more adequate to increase satiety in order to reduce weight, will be addressed. The next session will focus on food labels, teaching participants how to properly read and understand them, namely the ingredient lists and the nutritional composition tables (macro- and micronutrients). The tenth and 11th sessions will address the differences between several cooking methods and teach participants about the best method to decrease fat content and the best replacements to create low-calorie meals, which enhance their weight loss. In the last session, a dietitian will provide strategies to foster weight loss maintenance and a healthy lifestyle.

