#### 3.2.2. Combined Heart Rate and Motion Sensor

The Actiheart (Actiheart, CamNtech Limited, UK) is a lightweight (10 g) combined heart rate (HR) and movement (uniaxial accelerometer oriented to measure acceleration along the body’s longitudinal axis) sensor that utilizes both piezoelectric accelerometer and HR data synchronously. An individual calibration using a standardized step test will be realized. This test consists of step up and down a 15-cm high step, progressively increasing step frequency from 15 to 32.5 body lifts per minute (rate of change: 2.5 body lifts per min^2^). If some of the participants are not able to finish the step test, we will perform a group calibration that is available in the software (version 4.0.99). The Actiheart will be started in the long-term mode to record HR and acceleration with 15 s epochs. Participants will wear the Actiheart 24 h day−1 at the same time as the accelerometer and a valid day will be defined as having 600 or more minutes (≥10 h) of monitor wear during waking hours. Data from the Actiheart will be downloaded into the commercial software. The camNtech software algorithm allows data cleaning, recovering, and interpolation of missing and noisy HR. Using the raw data from the branched combined model that uses activity (acceleration) and HR, it is possible to extract and quantify the daily sedentary time (<1.5 METs). A break in sedentary time will be considered whenever participants are above the aforementioned cut-offs. Participants will also be instructed to register the periods in which they remove the device for water activities.

TEE will be predicted using the Crouter et al. equations [57]. Physical activity energy expenditure (PAEE) will be calculated as TEE minus (0.1 × TEE + REE), assuming the thermic effect of food represents 10% of TEE.

The delivery and fitting of the device to the participants will be conducted face-to-face [55]. The devices will be activated on the first day at 6.00 a.m. and data will be recorded in 15-sec epochs. Participants will be asked to record timing and reasons for every occasion the devices are removed.

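### The ActiGraph break rule leaves out interruptions of sitting that reach moderate or vigorous activity, and it disagrees with the Actiheart rule

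*Protocol article*

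**What the plan says.** Section 3.2.1 (Accelerometry) divides ActiGraph counts per minute into sedentary (<100), light (100–2019), moderate (2020–5998) and vigorous (≥5999), in order "to quantify the mean time in each intensity (sedentary, light, moderate, or vigorous". It then defines an ActiGraph break as "any bout of time in which the accelerometer count rises up to or above 100" counts/min, with a second condition: the bout must be one "which stays within the light-intensity physical activity (LIPA) range", given as below 2020 counts/min. No reason is stated for this ceiling.

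Section 3.2.2 (Combined Heart Rate and Motion Sensor) says of the Actiheart that "it is possible to extract and quantify the daily sedentary time (<1.5 METs"). It continues: "A break in sedentary time will be considered whenever participants are above the aforementioned cut-offs". No upper limit appears there. The same section has the Actiheart worn at the same time as the accelerometer.

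The Introduction names "free-living PA, sedentary time, energy balance regulation" among the secondary outcomes, and the Abstract lists sedentary behaviour as a secondary aim. Breaks are named as an outcome in neither place. Section 2.5 describes the content of the intervention: "Sedentary behavior will be the main topic of the sixth session, presenting strategies to reduce sedentarism", and in the session on being active, "some recommendations will be given in order to increase daily routine PA and structured physical activity".

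**The concern.** By the protocol's own cut-off, sedentary time ends when counts reach 100 per minute. Whether the person then strolls or walks briskly does not alter the fact that sitting was interrupted. The ActiGraph rule nevertheless recognises the interruption only when it stays light. One and the same event can therefore be a break on the Actiheart and not on the ActiGraph.

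What is at stake is the between-arm comparison of breaks, if it is made. Participants are enrolled because they fall short of moderate or vigorous activity thresholds (Table 2), and the programme encourages both routine and structured activity. If it works as intended, more interruptions in the intervention arm may reach 2020 counts/min, and those are the ones the rule discards. A real gain in breaks could then be understated.

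**Working it through.** There is no stated figure to reproduce. The check applies the rules to example bouts and then works out what the omission does to an arm difference.

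**Step 1: the rules on four example bouts.** The thresholds are those of section 3.2.1; the minute-by-minute counts are invented for illustration. Each sequence starts and ends in sedentary time (50 counts/min).

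| Bout (counts/min) | Rule as written, whole bout | Light minutes as their own bout | No upper limit |
|---|---|---|---|
| Light only: 50, 300, 900, 50 | break | break | break |
| Direct to moderate: 50, 2500, 3000, 50 | none | none | break |
| Light–moderate–light: 50, 500, 2600, 400, 50 | none | break | break |
| Vigorous: 50, 6500, 50 | none | none | break |

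The wording does not say how a bout is delimited. Under the stricter reading every interruption that reaches 2020 counts/min is lost. Under the looser one only direct moves from sedentary to moderate or vigorous are lost. Both readings drop some true interruptions.

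**Step 2: effect on the arm difference.** Let B be all interruptions per day in an arm and M the number the rule drops (those reaching ≥2020 counts/min on the stricter reading; direct transitions only on the looser one).

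- Recorded breaks in an arm = B − M.
- Recorded difference = (B_int − M_int) − (B_ctl − M_ctl).
- Bias = recorded difference − true difference = −(M_int − M_ctl).

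**Step 3: range.** The article gives neither B nor M, so all values here are assumptions. Control is fixed at B = 80 and M = 5, which gives 75 recorded.

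| B_int | M_int | True difference | Recorded difference | Bias |
|---|---|---|---|---|
| 85 | 4 | +5 | 81 − 75 = +6 | +1 |
| 85 | 5 | +5 | 80 − 75 = +5 | 0 |
| 85 | 7 | +5 | 78 − 75 = +3 | −2 |
| 85 | 10 | +5 | 75 − 75 = 0 | −5 |
| 85 | 12 | +5 | 73 − 75 = −2 | −7 |
| 80 | 10 | 0 | 70 − 75 = −5 | −5 |

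The rule fixes which bouts are dropped. The sign and size of the bias depend on M_int − M_ctl alone.

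**Step 4: what the rule does not touch.** Sedentary time is the time below 100 counts/min, and minutes per intensity come from the four bands; neither uses the break definition. The DXA outcomes do not use accelerometry.

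**The case against.** The strongest reply is that little depends on this rule. Breaks are not a named outcome, the Statistics section gives no analysis specific to them, and the outcomes that are named do not use the break rule. The Actiheart, worn concurrently, already supplies a break count without a ceiling, so a gain in breaks could still be seen there. The ActiGraph measure might also have been meant as a light-intensity break. The two devices work on different scales (vertical-axis counts against METs from heart rate and motion), so they would not agree exactly under any rule.

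Much of this stands, and it limits the scope. It does not remove the defect. The article defines breaks on both devices, so it evidently expects to derive them. The ActiGraph measure is not labelled as light-only, and nothing explains the ceiling. A second device with a different rule leaves two break counts that can diverge for a reason unrelated to the devices.

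A reader might go further and infer that the rule biases the result against the intervention. The documents do not support that as a fact. It is the expected direction if the programme raises moderate-to-vigorous interruptions more than control does. The article gives no break counts by arm, and the bias is zero if M is equal and favours the intervention if control has more such breaks.

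**Conclusion.** The point holds in limited form. As worded, the ActiGraph rule omits interruptions of sedentary time that go into moderate or vigorous activity (all of them, or only the direct ones, depending on how a bout is delimited), and it conflicts with the Actiheart rule in section 3.2.2. It may understate an intervention effect on breaks. The bias is −(M_int − M_ctl), which cannot be calculated from the article. The figures above, from +1 to −7 breaks/day, illustrate assumed inputs and are not estimates. The consequence is confined to the derived break variable and does not reach the primary outcomes or the named sedentary-time outcome.

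**What to change.** Rewrite the sentence in section 3.2.1 so that an ActiGraph break is any rise from below 100 to 100 counts/min or more, whatever intensity is then reached. All four example bouts in Step 1 then count, and in the Step 3 scenarios the recorded arm difference equals the true one. The rule would then share with section 3.2.2 the principle of having no upper limit, although counts and METs remain different scales. If light-only breaks are of interest, define them separately, say how a bout is delimited, label them as light-intensity breaks and report them beside all breaks.

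The cost is one sentence and re-processing of the same raw files. No new data or visits are needed. The change should be made before any comparison of breaks by arm.

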#### 3.2.2. Combined Heart Rate and Motion Sensor

The Actiheart (Actiheart, CamNtech Limited, UK) is a lightweight (10 g) combined heart rate (HR) and movement (uniaxial accelerometer oriented to measure acceleration along the body’s longitudinal axis) sensor that utilizes both piezoelectric accelerometer and HR data synchronously. An individual calibration using a standardized step test will be realized. This test consists of step up and down a 15-cm high step, progressively increasing step frequency from 15 to 32.5 body lifts per minute (rate of change: 2.5 body lifts per min^2^). If some of the participants are not able to finish the step test, we will perform a group calibration that is available in the software (version 4.0.99). The Actiheart will be started in the long-term mode to record HR and acceleration with 15 s epochs. Participants will wear the Actiheart 24 h day−1 at the same time as the accelerometer and a valid day will be defined as having 600 or more minutes (≥10 h) of monitor wear during waking hours. Data from the Actiheart will be downloaded into the commercial software. The camNtech software algorithm allows data cleaning, recovering, and interpolation of missing and noisy HR. Using the raw data from the branched combined model that uses activity (acceleration) and HR, it is possible to extract and quantify the daily sedentary time (<1.5 METs). A break in sedentary time will be considered whenever participants are above the aforementioned cut-offs. Participants will also be instructed to register the periods in which they remove the device for water activities.

TEE will be predicted using the Crouter et al. equations [57]. Physical activity energy expenditure (PAEE) will be calculated as TEE minus (0.1 × TEE + REE), assuming the thermic effect of food represents 10% of TEE.

The delivery and fitting of the device to the participants will be conducted face-to-face [55]. The devices will be activated on the first day at 6.00 a.m. and data will be recorded in 15-sec epochs. Participants will be asked to record timing and reasons for every occasion the devices are removed.

